In ADHD, the ability to control sensory processes and actions in a goal directed manner (Bunge et al., 2002) is severely compromised. ADHD patients are particularly impaired in different aspects of inhibition control, namely interference control, the suppression of task irrelevant, competing stimuli and response inhibition, the suppression of a prepotent response. Interference control has been repeatedly associated with the right inferior frontal gyrus (rIFG) (Luks et al., 2010; Zhu et al., 2010), a region that shows structural (Sowell et al., 2003; Durston et al., 2004) as well as functional alterations (Aron and Poldrack, 2005) in ADHD patients. For example, unmedicated ADHD patients showed less activity in the rIFG during an inhibitory task than healthy controls (Rubia et al., 2011), but reached age adequate levels when medicated (Lee et al., 2010). Since tDCS over of the rIFG and the pre-supplementary motor area had been successfully used to improve response inhibition in healthy adults (Hsu et al., 2011; Jacobson et al., 2011; Ditye et al., 2012), Breitling et al. (2016) chose to apply tDCS over the rIFG in adolescents with (and without) ADHD during a Flanker task, targeting interference control. They showed that anodal tDCS over the right IFG improved interference control and reduced reaction time variability compared to ADHD patients receiving sham stimulation (Breitling et al., 2016). In this study, a post-hoc simulation of current density concentrations within the brain revealed very little focal but a widespread current density distribution. This is a problem in most conventional tDCS set-ups, where large pad electrodes are used (bipolar montage), making it difficult to judge whether stimulation effects result from anodal stimulation of the target region or cathodal stimulation of the so-called reference or return electrode. Current recommendations (Woods et al., 2016) therefore advocate the use of optimized multi-channel montages.

In the current protocol, we aim to investigate in two separate studies how optimized multi-channel stimulation of the left dlPFC (**Study A**) and stimulation of the rIFG (**Study B**) improves relevant cognitive functions and clinical measures in children and adolescents with ADHD. These studies will be conducted within the framework of the STIPED (Stimulation in Pediatrics) consortium.

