#### 2.2.2 Secondary endpoints

- Severity of ADHD symptoms (inattention, hyperactivity/impulsivity): changes from screening/ V0 to V11 and V12
- **Study A:** Reaction time and reaction time variability in n-back task, number of omission and commission errors: changes from V0 to V11 and V12  
**Study B:** Reaction time and reaction time variability in Flanker task, number of omission and commission errors in congruent and incongruent trials: changes from V0 to V11 and V12
- Performance measures in neuropsychological tasks that assess impaired functions in ADHD but are different from the task presented during stimulation accuracy and reaction times / reaction time variability in  
**Study A:** (1) Flanker task and (2) and a Continuous Performance task (CPT): changes from V0 to V11 and V12  
**Study B:** (1) n-back working memory task and (2) and a Continuous Performance task (CPT): changes from V0 to V11 and V12
- Functional brain related outcome measures (1) *resting state EEG*: connectivity, phase coherence, Granger causality (2) *event related potentials*: amplitude, latency, latency variability, neuronal sources of task relevant components: changes from V0 to V11 and V12 (3) *resting state fMRI*: changes from V0 to V11
- Quality of life: changes from Screening/V0 to V12

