## 11.1 Sample size calculation

The sample size for **Study A** and **Study B** is calculated separately for each study using a two-sided t-test (significance level  $\alpha=0.05$ ) with a power  $1-\beta=80\%$  based on a medium expected effect size of  $d=0.6$ . Previous studies in ADHD have shown similar or larger effect sizes for tDCS. This result leads

to a required sample size of 45 patients per group (G\*Power3.1); assuming 10% drop-out, the total sample size consists of 200 randomized patients (100 patients for each study). In **Study A**, 50 patients will be allocated randomly to Arm A, whereas the remaining 50 patients will be randomized to Arm B. The same procedure will be repeated for **Study B**.

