### Study B:

In the **flanker task** (target task), stimuli consist of five arrows. The middle arrow is the target stimulus and participants should indicate via button press with the right or with the left hand if the target arrow points to the right or to the left. The outer arrows serve as distractors and can point in the same direction (congruent trial) or in the opposite direction (incongruent trial). The flanker task provides information on cognitive interference control.

The primary endpoint for Study B is the **overall accuracy** (i.e., correct hits for congruent and incongruent trials in percent, variable *flanker\_oa*) in the flanker task. Effectiveness of anodal tDCS stimulation will be evaluated by analyzing patients' performance at Visit V11 (T3: Post; see Figure 1), adjusted for performance at Visit V0 (T2: Baseline).

For both **study A** and **study B**, safety and tolerability of tDCS assessed by (1) a standardized safety questionnaire as well as (2) EEG recordings before and after tDCS (EEG abnormalities such as slowing under the stimulating electrode or in remote brain areas, polarization asymmetries, spike-and-wave discharges) and (3) number, type, and severity of adverse events (AEs, variables *ad*, *ad\_type*, and *ad\_sev*) and severe adverse events (SAEs, variables *sae*, *sae\_type*, and *sae\_sev*) are defined as primary endpoints.

***Note: Statistical analyses for raw EEG recordings are not included in this SAP. No raw EEG data will be analyzed by the IMIS. However, defined aggregated EEG data (defined abnormalities coded e.g., in SPSS files) as relevant for safety will be analyzed.***

As an overall safety analysis of all STIPED studies, the safety endpoints ((S)AEs and safety questionnaire) will also be analyzed for Study A and Study B together (and furthermore also together with the safety data of the other studies in WP3, WP4 and WP5, details of this analysis will be specified elsewhere) in order to get a global safety assessment of tDCS in children and adolescents.

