The Continuous Performance Task (CPT) is the **second non-target task** in Study A. In the CPT, various upper case letters will be presented. One of the letters will be defined as a cue and one as a target stimulus. Whenever the cue is followed by the target stimulus, participants are instructed to press a button. However, participants should withhold their response if the cue is followed by another stimulus. Secondary endpoints at V11 and V12 for Study A in the CPT are:

- The **overall accuracy** (i.e., sum of correct neutral, correct cues, correct non-targets, and correct targets, variable *CPT\_oa*) in the CPT.
- The **reaction time** (variable *CPT\_rt*) for the overall accuracy in the CPT.
- The **variability of the reaction time** for the overall accuracy (i.e., standard error, variable *CPT\_rtSD*) in the CPT.
- All **omission errors** (i.e., sum of all missed targets, variable *CPT\_omiss*) in the CPT.
- All **commission errors** (i.e., sum of all false alarms, false alarms for cues, and false alarms for non-targets, variable *CPT\_comiss*) in the CPT.

Secondary endpoints at V11 and V12 for **Study B** in the **target task** (flanker task) are:

- The **reaction time** (variable *flanker\_rt*) for the overall accuracy in the flanker task.
- The **variability of the reaction time** for the overall accuracy (i.e., standard error, variable *flanker\_rtSD*) in the flanker task.
- All **omission errors** (i.e., sum of all omission errors for congruent and incongruent trials, variable *flanker\_omiss*) in the flanker task.
- All **commission errors** (i.e., sum of all commission errors for congruent and incongruent trials, variable *flanker\_comiss*) in the flanker task.

Secondary endpoints at V11 and V12 for **Study B** in the **first non-target task** (n-back working memory task) are:

- The **overall accuracy** (i.e., sum of correct hits, correct rejections, correct rejections 1lure, and correct rejections 2lure in percent, variable *nback\_oa*) in the n-back working memory task.
- The **reaction time** (variable *nback\_rt*) for the overall accuracy in the n-back working memory task.
- The **variability of the reaction time** for the overall accuracy (i.e., standard error, variable *nback\_rtSD*) in the n-back working memory task.
- All **omission errors** (i.e., sum of all missed target trials, variable *nback\_omiss*) in the n-back working memory task.

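### Every Study B Flanker endpoint pools congruent and incongruent trials, so no planned behavioural analysis separates interference control from general attention

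*Combined protocol and SAP*

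**What the plan says.** The target of Study B is stated plainly. Protocol 1.1 bases it on a previous rIFG study in adolescents with ADHD: "They showed that anodal tDCS over the right IFG improved interference control and reduced reaction time variability". SAP 6.2, under Study B, says "The flanker task provides information on cognitive interference control". Protocol 7.3 describes the task: the distractor arrows either agree or disagree with the target arrow, and the two trial types are split 50:50.

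The SAP defines five Flanker variables for Study B:

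- flanker_oa (primary, SAP 6.2): percentage correct over congruent and incongruent trials together.
- flanker_omiss (SAP 6.3): omissions summed over both trial types.
- flanker_comiss (SAP 6.3): "sum of all commission errors for congruent and incongruent trials, variable" flanker_comiss.
- flanker_rt and flanker_rtSD (SAP 6.3): one variable each, tied to overall accuracy, with no split by trial type.

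SAP 7.4 analyses each secondary outcome with the regression of SAP 7.3, exchanging only the dependent variable and its baseline.

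Protocol 2.2.2 words the Study B error endpoints as "number of omission and commission errors in congruent and incongruent trials: changes from V0 to V11 and V12". The corresponding Study A line for the n-back task has no such qualifier.

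**The concern.** Interference arises only when the distractors conflict with the target. Isolating it needs either the incongruent trials on their own or the contrast between incongruent and congruent trials. The SAP plans neither, and no model has an arm-by-congruency term.

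Two results would then be hard to read. A gain in pooled accuracy could reflect better conflict handling, better general attention, or slower and more careful responding. A null result could conceal an effect limited to conflict trials. SAP 7.3 puts the emphasis on effect sizes, yet the size of the effect on the targeted function would not be among the planned estimates. If a congruency analysis were added after unblinding, it would be post hoc.

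**Working it through.** **1. Is there any congruency-specific measure?** The five Flanker variables listed above are all pooled. The other Study B behavioural endpoints come from the n-back and CPT, which SAP 6.3 labels non-target tasks. The EEG and MRI readouts are outside the SAP and name no congruency contrast. So no planned behavioural analysis in the SAP isolates interference.

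**2. Are the data there?** Protocol 7.3 gives 184 trials per block and two blocks at V0, V11 and V12. That is 2 × 184 = 368 trials per visit, or 184 of each type. Protocol 8.1 says the log files record the nature and occurrence of every event.

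**3. The plan's own sample size.** Protocol 11.1 says the size "is calculated separately for each study using a two-sided t-test", with alpha 0.05, power 80% and d = 0.6. The noncentral t calculation gives n = 44.59, hence the "required sample size of 45 patients per group" (power 80.4%). With 10% drop-out, 45 / 0.9 = 50 per arm, 100 per study and 200 in all. The figure reproduces. The d of 0.6 is not tied to any particular Flanker measure.

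**4. What pooling does to an effect on conflict trials only (illustration).** With a 50:50 mix, pooled accuracy = (congruent + incongruent) / 2, so a raw gain Δ on incongruent trials alone becomes Δ/2. Let r be the congruent SD divided by the incongruent SD, and ρ the correlation of the two accuracies. Neither is in the documents; I assume r = 0.5 to 1 and ρ = 0.3 to 0.9. Then

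d_pooled = 0.5 × d_inc / [0.5 × √(1 + r² + 2ρr)].

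With d_inc = 0.6 (also an assumption), 45 per arm and no baseline adjustment:

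| r | ρ | d_pooled | power |
|---|---|---|---|
| 0.5 | 0.3 | 0.48 | 62% |
| 0.5 | 0.9 | 0.41 | 48% |
| 1 | 0.3 | 0.37 | 42% |
| 1 | 0.9 | 0.31 | 30% |

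Incongruent accuracy analysed on its own would have 80%.

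**5. The opposite case.** If both trial types gain equally and r = 1, d_pooled = 0.6 / √((1 + ρ)/2). For ρ = 0.3 to 0.9 this is 0.74 to 0.62, with power 94% to 82%. Pooling then costs nothing.

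**6. The interference cost.** For an effect on incongruent trials only, d_diff = d_inc / √(1 + r² − 2ρr). Over the same ranges this is 0.51 to 1.34, with power 66% to above 99%. At r = 1 and ρ = 0.3 the difference score (0.51) is less sensitive than incongruent accuracy alone (0.60), which is a reason to prespecify both.

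**The case against.** The strongest reply is that overall accuracy is a deliberate and consistent choice. It is the Study B primary endpoint in the synopsis, Protocol 2.2.1 and 11.3.3, and SAP 6.2 and 7.3. Half of its trials are incongruent, so it does respond to interference control. That stands, and nothing here asks for the primary endpoint to change.

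Four stronger readings are tempting, and the documents do not support them.

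- *The SAP contradicts the protocol.* A reader might take the phrase in Protocol 2.2.2 as separate counts by trial type, since for Study B it would otherwise add nothing. But it can also mean a total over both types; Protocol 8.1 uses a similar construction for overall accuracy. The SAP resolves an ambiguous phrase as a sum. The phrase covers errors only, and separate counts would still not define a contrast.
- *Study B is underpowered.* The 30% to 62% comes from placing d = 0.6 on the incongruent trials and assuming no congruent effect. Protocol 11.1 does neither. Baseline adjustment would also raise power: with r = 1, ρ = 0.3 to 0.7 and an assumed baseline correlation of 0.5, 42% to 33% becomes 52% to 42%. Adding secondary endpoints does not alter the power of the primary.
- *Study B can say nothing about specificity.* Flanker reaction time bears on a speed-accuracy shift, and a Flanker gain without an n-back or CPT gain would argue against general alertness. This evidence is useful but indirect; none of it isolates conflict.
- *SAP 7.3 changed the construct.* It names response inhibition, which Protocol 1.1 distinguishes from interference control. But Protocol 2.2.1 uses the joint label inhibitory/interference control, and SAP 6.2 names interference control. This is loose wording.

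A further objection concerns multiplicity. Study B already has 29 task-based secondary models (14 variables at two visits, plus flanker_oa at V12), with no multiplicity control described. Splitting every Flanker measure would add many more, so the addition should be kept small.

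**Conclusion.** The point holds as a gap in the secondary endpoints. Pooling is explicit for accuracy, omissions and commissions; for reaction time and its variability it is inferred from the single variable names and their link to overall accuracy. As the SAP stands, Study B can estimate an effect on Flanker performance but has no prespecified behavioural estimate specific to interference control.

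The halving of an effect confined to incongruent trials follows from the 50:50 mix alone. The power figures are illustrative and rest on the assumed d, SD ratio and correlation and on the absence of any congruent effect. They are not a deficit in the planned 80%. The conclusion does not depend on them: it rests on the endpoint definitions and the missing congruency term.

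**What to change.** Keep pooled overall accuracy as the Study B primary endpoint. Before unblinding:

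- Add three secondary endpoints to SAP 6.3 for the Study B Flanker task at V11 and V12: incongruent-trial accuracy, and the interference cost (incongruent minus congruent) for accuracy and for reaction time.
- Analyse each in the same ANCOVA with its own T2 baseline, and label them as secondary without multiplicity control.
- Report omission and commission errors by trial type, descriptively. This also meets the by-condition reading of Protocol 2.2.2.
- State in SAP 6.3 that flanker_rt and flanker_rtSD are pooled over trial type, if that is the intention.
- Replace response inhibition with interference control for Study B in SAP 7.3.

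The cost is a few derived variables from existing log files and 3 × 2 = 6 more models on top of 29, or 6/29 = 21%. The downside is somewhat more unadjusted secondary testing. No new data, visits or participants are needed.

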## 7. Statistical analyses

Each of the two studies (**Study A:** left dlPFC; **Study B:** rIFG) will be analyzed separately. Before the statistical analyses of primary and secondary outcomes in **Study A** and **Study B**, empirical data will be checked for plausibility (e.g., detecting unrealistic values). This step also includes outlier detection.

### 7.1 Outliers

An *outlier* is an observation that lies an abnormal distance from other values in a random sample from a population. Any kind of outliers (i.e., mild or extreme) will be identified before primary analyses. Without breaking the blinding, we will calculate descriptive statistics for all primary and secondary endpoints. Outliers will be visualized with scatter plots and box plots. Without breaking the blind, any outliers (in both study arms) will be handled in the same way: for data that is available in other records (e.g. demographic or clinical data available in clinical records), a query will be sent to the center to verify and confirm or correct the outlier. For values only available as source data (e.g. neuropsychological performance measures), it will be determined together with the coordinating investigator whether outliers may represent extreme but true values (which will be analyzed as such), or are so implausible that they represent measurement error (which will be removed from the data set). In particular for the primary outcome measures only clear measurement errors will be removed.

The box plot is a useful graphical display for describing the behavior of the data in the middle as well as at the ends of the distributions. The box plot uses the median and the lower and upper quartiles (defined as the 25th and 75th percentiles). If the lower quartile is Q1 and the upper quartile is Q3, then the difference (Q3 - Q1) is called the interquartile range or IQ. A box plot is constructed by drawing a box between the upper and lower quartiles with a solid line drawn across the box to locate the median. The following quantities (called fences) are needed for identifying outliers in the tails of the distribution:

1. lower inner fence:  $Q1 - 1.5 \cdot IQ$

2. upper inner fence:  $Q3 + 1.5 \cdot IQ$
3. lower outer fence:  $Q1 - 3 \cdot IQ$
4. upper outer fence:  $Q3 + 3 \cdot IQ$

A point beyond an inner fence on either side is considered a mild outlier. A point beyond an outer fence is considered an extreme outlier.

As an example, a SPSS syntax code for outlier detection is shown in Appendix 3. Here, outlier detection is conducted for the primary outcome in **Study A** (overall accuracy in the n-back working memory task, variable *nback\_oa*).

## 7.2. Demographic and baseline characteristics

Demographic and baseline characteristics recorded at Visit 1.0 (before any stimulation, see Figure 1) will be analyzed with descriptive statistics. Sample characteristics will be reported for the full study sample as well as for each study arm separately.

For the categorical variables *gender*, *ethnicity*, *substance consumption*, *socioeconomic status*, *handedness*, *pubertal development*, and *pregnancy* we will report absolute and relative frequencies in tables and figures (see Table 1 in Appendix 1). For metric variables with a continuous scale (*age*, *height*, *weight*, *psychiatric assessment*, *social responsiveness*, *intelligence*, *arousal*, and *motivation*) we will report means, medians, standard deviations, and interquartile ranges. We will visualize empirical results with box plots and scatter plots, where appropriate.

## 7.3. Primary endpoints

To test potential effects of tDCS (anodal tDCS vs. sham stimulation) on working memory (**Study A**), or response inhibition (**Study B**), statistical analyses will be performed separately for each study. Primary endpoints will be the overall accuracy in the n-back working memory task (**Study A**), the overall accuracy in the flanker task (**Study B**).

For both study arms, the primary outcome of interest will be measured at the end of the intervention at T3 (Visit 11, variables with suffix *\_T3*). Regarding these outcome variables, possible differences between anodal tDCS and sham stimulation will be tested using an analysis of covariance. In general, this is a regression model with one dependent outcome variable and several independent variables. Analyses will be performed separately for **Study A** and **Study B**. For **Study A**, the outcome variable in this model will be the overall accuracy in the n-back working memory task (*nback\_oa\_T3*). For **Study B**, it will be the overall accuracy in the Flanker task (*flanker\_oa\_T3*). In both models, we use the binary variable *stimulation* (coded as 1=anodal tDCS stimulation and 0=sham stimulation) as independent variable. Additionally, we will enter the (dummy-coded) variables *center*, *sex* (1=female, 0=male), *puberty status*, *age*, *IQ*, and the *baseline value* of accuracy in the respective tasks at T2 (Visit 0, variables with suffix *\_T2*) as covariates into this model. Hence, we control for their possible effects on the primary outcome variables and calculate adjusted regression coefficients. In this study, randomisation was stratified by center, thus it is necessary to account for the center-effects in the analysis as well. This is because stratified randomisation leads to correlation between treatment arms, making it necessary to adjust for the

stratification factors in the analysis to obtain correct confidence intervals and p-values, maintain the type I error rate at its nominal level (usually set at 5%), and avoid a reduction in power (Kahan & Morris 2013 and ICH E9 guideline). Therefore *center* will be used as a fixed effect in the analysis. Similarly, since the baseline value is strongly related to outcome for the neuropsychological measures used here, this *baseline value* will be used as a covariate in the analysis. Further, it seems plausible that *sex* (1=female, 0=male), *puberty status*, *age* and *IQ* are related to neuropsychological performance, however this effect might already be sufficiently captured by the baseline values of performance and additionally, *puberty status* and *age* can be expected to be correlated. Thus the effects of these covariates will first be investigated in a blinded manner in a model without *stimulation* before a decision is made whether to include them in the final model.

As an example, a SPSS syntax code for the planned statistical analyses is shown in Appendix 4. Here, the regression analysis is conducted for the primary outcome in **Study A** (overall accuracy in the n-back working memory task, variable *nback\_oa\_T3*).

Results (e.g., standardized and unstandardized regression coefficients, standard errors, confidence intervals, and p-values) will be presented and summarized in tables and figures (for an example see Table 3 in Appendix 5). If the regression coefficient for *stimulation* is positive and has a p-value <0.05, superiority of tDCS over sham will be concluded. As this is a phase II trial, emphasis will be on effect size estimates and corresponding 95% confidence intervals. Empirical results based on the ITT set will be assured with sensitivity analyses (i.e., validation in the PP set).

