## 11.2 Randomisation

Randomisation will be carried out with respect to the randomisation protocols. Each patient will be allocated randomly to one of the two studies (**Study A** or **Study B**) and to one of the two treatment conditions (anodal tDCS stimulation or sham stimulation). Randomisation will be stratified for the variables clinical center (Coimbra, Frankfurt, Kiel/ZIP, Kiel/UKSH or Magdeburg), and gender (male or female). Experimental conditions will be block randomized. Each block will have a length of four and, thus, will assign a total of four patients to the different treatment conditions (**Study A** + tDCS, **Study A** + sham, **Study B** + tDCS, and **Study B** + sham). Block randomization will be done with the electronic randomization tool BiAS for Windows (version 11, 2016). Randomisation will be performed by IMIS/ZKS.

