### 11.3.3 Data analysis

#### *Primary Outcome*

We will test for a difference in the primary outcome measure at T3 (Visit 11; **Study A**: overall accuracy in an *n-back* task at the end of the intervention; **Study B**: overall accuracy in the *Flanker* task at the end of the intervention) using an analysis of covariance with covariates center, sex, puberty status, age, IQ, and the baseline value of accuracy in the respective tasks at T2 (Visit 0). Emphasis will be on the 95% confidence intervals of the effect size estimates; additionally, p-values will be calculated. Analyses will be performed separately for **Study A** and **Study B**.

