| - concurrent pharmacological treatment of ADHD                                                                                                                | exclusion_11  |

*Note:* Variables listed in the second column of this table will be dichotomous (1=fulfilled, 0=not fulfilled).

### 10.3 Appendix 3

```
DESCRIPTIVES VARIABLES= nback_oa  
/STATISTICS=MEAN STDDEV MIN MAX.
```

```
FREQUENCIES VARIABLES= nback_oa  
/NTILES=4  
/STATISTICS=STDDEV VARIANCE RANGE MINIMUM MAXIMUM MEAN MEDIAN  
/ORDER=ANALYSIS.
```

```
EXAMINE VARIABLES= nback_oa  
/PLOT NONE  
/PERCENTILES(5,10,25,50,75,90,95) HAVERAGE  
/STATISTICS DESCRIPTIVES EXTREME  
/CINTERVAL 95  
/MISSING LISTWISE  
/NOTOTAL.
```

```
EXAMINE VARIABLES= nback_oa  
/PLOT=BOXPLOT  
/STATISTICS=NONE  
/NOTOTAL  
/ID=vp_nr.
```

*Note:* This is an example for outlier detection conducted in the statistical software SPSS for Windows. The SPSS syntax code checks the primary outcome in **Study A**, the overall accuracy in the n-back working memory task (variable *nback\_oa*), with descriptive statistics and boxplots for plausibility reasons.

## 10.4 Appendix 4

```
REGRESSION
/DESCRIPTIVES MEAN STDDEV CORR SIG N
/MISSING LISTWISE
/STATISTICS COEFF OUTS CI(95) R ANOVA
/CRITERIA=PIN(.05) POUT(.10)
/NOORIGIN
/DEPENDENT nback_oa_T3
/METHOD=ENTER
stimulation
center
sex
*puberty status
age
IQ
nback_oa_T2
.
```

Note: This is an example for the primary outcome analyses in the statistical software SPSS for Windows. The SPSS syntax code shows a regression analysis with the primary outcome in **Study A** (overall accuracy in the n-back working memory task, variable *nback\_oa\_T3*) as dependent variable. The variables *stimulation* (coded as 1=anodal tDCS stimulation and 0=sham stimulation), *center*, *sex*, *puberty status* (only to be included if correlation with age is not too large), *age*, *IQ*, and the baseline value of accuracy in the respective tasks at T2 (Visit 0, *nback\_oa\_T2*) enter the regression model as independent variables.

## 10.5 Appendix 5

Table 3 below illustrates how empirical results of primary outcome analyses will be summarized. Here, some fake results of **Study A** are presented. Model results of **Study B** will be presented in a similar way.

Table 3

*Model results for Study A*

| Model          | IV               | b | S.E. | CI [ b ] | $\beta$ | p |
|----------------|------------------|----------|------|-----------------|---------|----------|

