| Study A | stimulation      | xxx      | xx   | xxx             | xxx     | xxx      |
|                | center A         | xxx      | xx   | xxx             | xxx     | xxx      |
|                | sex              | xxx      | xx   | xxx             | xxx     | xxx      |
|                | *puberty status  | xxx      | xx   | xxx             | xxx     | xxx      |
|                | age              | xxx      | xx   | xxx             | xxx     | xxx      |
|                | IQ               | xxx      | xx   | xxx             | xxx     | xxx      |
|                | overall accuracy | xxx      | xx   | xxx             | xxx     | xxx      |
|                | n-back at T2     |          |      |                 |         |          |

*Notes.* *N* = [\*insert sample size\*]; stimulation (1=anodal tDCS stimulation, 0=sham stimulation), center A (1=yes, 0=no), sex (1=female, 0=male), IV = independent variable; *b* = unstandardized regression weight; S.E. = standard error; CI [*b*] = confidence interval for unstandardized regression weight;  $\beta$  = standardized regression weight; *p*=p-value.

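### SAP 7.3 makes sex, a randomisation stratum, an optional covariate in the primary model, and the SAP's text, example syntax and results table disagree on how centre is coded

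*Combined protocol and SAP*

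**What the plan says.** **Randomisation.** Protocol 11.2: "Randomisation will be stratified for the variables clinical center (Coimbra, Frankfurt, Kiel/ZIP, Kiel/UKSH or Magdeburg), and gender (male or female". Blocks of four cover the four study-by-arm conditions, so each complete block gives each study one tDCS and one sham patient of the same centre and sex.

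**Primary model in the protocol.** Section 11.3.3 tests the difference at T3 "using an analysis of covariance with covariates center, sex, puberty status, age, IQ, and the baseline value of accuracy" at T2. No covariate is conditional.

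**Primary model in the SAP.** Section 7.3 first lists the same covariates. It then gives the reason for adjusting: "In this study, randomisation was stratified by center, thus it is necessary to account for the center-effects in the analysis as well". It adds that correct intervals, p-values and type I error depend on adjusting for the stratification factors. Only centre and the baseline value are then made firm. Sex, puberty status, age and IQ are to be examined blinded, in a model without stimulation, "before a decision is made whether to include them in the final model". No decision rule is stated.

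**Appendix 4.** The note marks only puberty status as conditional ("only to be included if correlation with age is not too large", with no threshold) and lists sex without condition.

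**Coding of centre.** SAP 7.3 says dummy-coded and fixed effect. The Appendix 4 example enters one variable named center in SPSS REGRESSION. Table 3 in Appendix 5 has one centre row, noted as "center A (1=yes, 0=no". SAP 7.4 reuses the Appendix 4 syntax for every secondary outcome and changes only the dependent variable and its baseline.

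**The concern.** Blocking on centre and sex makes the arms more alike than simple randomisation would. The estimated treatment difference then varies less from trial to trial. A model that leaves out a prognostic stratum does not credit this: the stratum's variance stays in the residual, and the reported standard error exceeds the true one. This trial places its emphasis on effect sizes and 95% confidence intervals, so needlessly wide intervals affect its main output.

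The SAP gives this argument itself but applies it to one of the two strata. As a result the primary model has three versions: all covariates fixed (protocol 11.3.3 and the first list in SAP 7.3), four covariates optional (later in SAP 7.3), or one optional (Appendix 4).

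The centre coding raises a related problem. SPSS REGRESSION has no handling of categorical variables. A numeric centre code entered as printed would be fitted as one slope across the code numbers, in the primary model and, through SAP 7.4, in each secondary one.

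**Working it through.** **1. The plan's own figure.** Protocol 11.1 sizes each study "using a two-sided t-test", "based on a medium expected effect size of" 0.6, with alpha 0.05 and power 80%. Exact noncentral-t power is 79.5% at 44 per group and 80.4% at 45, so 45 is confirmed. 45 / 0.90 = 50 per arm, or 100 per study. Nothing below changes this.

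**2. Effect of dropping sex.** Let s be the share of residual variance (after the other covariates) that sex explains. Because sex is balanced by design, the true standard error is unchanged, but the reported one is multiplied by

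R = 1 / √(1 − s).

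The actual type I error is about 2 × [1 − Φ(1.96 R)]. The documents give no value for s, so this is a range:

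| Assumed s | R | SE overstated by | Type I error |
|---|---|---|---|
| 0 | 1.000 | 0% | 5.0% |
| 5% | 1.026 | 2.6% | 4.4% |
| 10% | 1.054 | 5.4% | 3.9% |
| 20% | 1.118 | 11.8% | 2.8% |

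**3. Check by simulation.** There were 3000 runs per scenario with N = 100, centre sizes 30/20/12/13/25 (protocol 5.3), 20% girls (the 4:1 ratio in protocol 5.2) and 1:1 pairs within centre-by-sex strata. Assumptions not in the documents are a baseline correlation of 0.6 (residual variance 1 − 0.36 = 0.64), the size of the sex effect δ, no centre effect, and a true d of 0.4 for power, chosen so that differences are visible. A sex effect δ adds δ² × 0.2 × 0.8 to the variance, so R = √[(0.64 + 0.16 δ²) / 0.64].

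| δ (SD) | R by formula | Simulated type I error without sex | Power at d = 0.4, with sex → without |
|---|---|---|---|
| 0 | 1.000 | – | 69.7% → 69.7% |
| 0.3 | 1.011 | 4.6% | 68.4% → 67.6% |
| 0.6 | 1.044 | 4.3% | 69.1% → 66.1% |
| 1.0 | 1.118 | 2.8% | 68.8% → 59.8% |

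Simulated mean standard errors agree with the formula: 0.168 / 0.161 = 1.043 at δ = 0.6, and 0.180 / 0.161 = 1.118 at δ = 1.0. With centre dummies and sex always in the model, type I error was 4.5% to 5.8% over all scenarios (simulation error about 0.4 points).

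**4. Centre, only if the Appendix 4 line were run as printed.** Five centres need 5 − 1 = 4 dummies; one slope uses one. If centre effects have no particular order, a slope picks up roughly a quarter of the between-centre variance and three quarters stays in the residual. With an assumed centre share of 20%:

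R = √[(0.80 + 0.75 × 0.20) / 0.80] = √(0.95 / 0.80) = 1.09.

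Simulation gave 0.179 → 0.194 (+8%), type I error about 3.1% to 3.4%, and power at d = 0.6 falling from 0.91 to 0.88. With a 10% share, R = √(0.975 / 0.90) = 1.04. If sex (5%) were also dropped alongside a 20% centre share, R = √(0.95 / 0.75) = 1.125, with simulated power at d = 0.6 of 0.88 to 0.89.

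**5. The passages on centre.** The text says dummies. Table 3's single row is a 0/1 indicator, so it is a dummy but three short. Only the Appendix 4 line could be read as a numeric code.

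**The case against.** A good deal can be said for the plan.

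- **The check is blinded and excludes stimulation.** A reader might infer that covariates could be chosen to favour tDCS. The procedure as written cannot select on the treatment effect. It might also be inferred that the blind is unsafe, because protocol 7.1.2 gives a statistician the stimulation file names. That passage concerns preparing the allocation material, and nothing says the same person runs the covariate check.
- **The error is conservative.** No false-positive risk arises. Even with both faults, simulated power at d = 0.6 stays above the planned 80%, for N = 100 without drop-out.
- **Sex may well be kept.** At s = 5% and N = 100 its expected t-value is about √(100 × 0.05 / 0.95) = 2.3, and if s is near zero, dropping it costs nothing. With no stated criterion, though, neither outcome can be predicted from the SAP.
- **Centre is specified in the governing text.** A reader of Appendix 4 might infer that a linear centre term is planned. The documents do not support that: SAP 7.3 says dummy-coded and fixed effect, the syntax is labelled an example and contains a placeholder for puberty status, and Table 3 shows a dummy. The 8% to 12% figures in step 4 are therefore not the expected cost of this plan.

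What remains is the treatment of sex, which departs from the protocol and from the SAP's own argument, and an inconsistency in illustrations that SAP 7.4 reuses.

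**Conclusion.** The point holds for sex. Sex is a randomisation stratum and an unconditional covariate in the protocol. The SAP does not name it as a stratum and makes its inclusion depend on an unspecified rule. If it is prognostic and dropped, the interval for the treatment effect is wider than it should be: about 2.6% at an assumed 5% share of residual variance, with a range from nothing to about 12% at a 20% share. With roughly 20% girls and baseline performance already in the model, the lower part of that range is the more plausible, but the documents give no figure.

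For centre, the finding is an inconsistency between the SAP text, Appendix 4 and Table 3 that needs reconciling. It does not show that the wrong model will be fitted.

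The severity is moderate to low. The sample size, the conduct of the trial and the control of type I error are unaffected.

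**What to change.** - **SAP 7.3:** state that randomisation was stratified by centre and sex, and that both always stay in the primary and secondary models. Limit any blinded check to puberty status, age and IQ. Whether those three are fixed as in the protocol or checked is a trade-off; if checked, state the criterion, including a threshold for the correlation between age and puberty status.
- **Appendix 4:** enter centre as a factor (for example with UNIANOVA) or as k − 1 dummies, and make the note on conditional covariates agree with 7.3. Here k is the number of centres that randomised patients. Amendment 1 replaced the Kiel UKSH site with Bielefeld, and the documents do not say whether UKSH had already randomised anyone, so k is five or six.
- **Appendix 5, Table 3:** show all centre rows.

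The cost is one degree of freedom for sex, some SAP wording and a few lines of syntax. In the simulation with no sex effect, keeping sex left power unchanged at 69.7%.
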